## Abstract

**Background:**

Problems with oral language skills in childhood have been linked with poor educational, employment, and mental health outcomes. In the UK, there is increasing concern about the oral language skills of children, particularly children from areas of social disadvantage. Research emphasises the importance of the home language environment as a fundamental bedrock for the development of oral language skills. It is vital, therefore, that support is available to help families in need to provide the optimal language environment for their child. Talking Together is a 6-week home visiting programme recently commissioned by Better Start Bradford to develop parents’ knowledge of the importance of a good language environment and help to improve parent-child interactions. This study represents the initial steps in developing a definitive trial of the Talking Together programme.

**Method:**

This study is a two-arm randomised controlled feasibility study in which families referred into the Talking Together programme and consent to participate in the trial will be randomly allocated to either an intervention group or a waiting control group. We will assess the recruitment and retention rates, the representativeness of our sample, the appropriateness of our measures, and the sample size needed for a definitive trial. We will also carry out a qualitative evaluation to explore the acceptability of trial procedures for families and service providers, fidelity of delivery, time and resources for training, and barriers and facilitators to engagement with the programme. Clear progression criteria will be used to assess suitability for a definitive trial.

**Conclusion:**

This feasibility study will inform the development of a definitive trial of this home-based visiting programme, which will add to the sparse evidence base on which practitioners can draw when supporting families in need. The lessons learnt from this feasibility study will also inform the wider evaluation work of the Better Start Bradford Innovation Hub.

**Trial registration:**

The trial is registered with the ISRCTN registry: study ID ISRCTN13251954. Date of registration: 21 February 2019 (the trial was retrospectively registered).

## Background

Over the past 10 years, a number of reports have raised concerns about the oral language skills of children in the UK. In particular, it is estimated that speech, language, and communication difficulties can affect up to 50% of children from more deprived backgrounds across the UK [1]. Strong language skills underpin children’s educational achievement and have been found to be predictive of both social and scholastic success [2, 3]. Moreover, early language difficulties have been linked to poor adult mental health outcomes, particularly anxiety and social phobia [4]. There is therefore clearly a national interest in considering what can be done to support early language development, particularly in children from deprived backgrounds. Unfortunately, the recent Bercow 10 report [1] suggests that not enough is being done to address children’s language needs and the Early Intervention Foundation (EIF) recently suggested that language should be a public health issue [4]. Indeed, the EIF suggest that ‘Child language is similar to obesity and other risk factors (such as mental health and diet) in terms of its impact on children’s overall wellbeing’ [4] (page 36). Research identifies the home learning environment as the bedrock for children’s early language development [2, 5], and it is therefore vital to support families in need to foster positive parent-child interactions and supportive home environments that enrich children’s early language learning opportunities. Moreover, it is important that practitioners working with families have access to high-quality evidence-based programmes in order to ensure they can provide the most effective means of support [6]. Unfortunately, few such evidence-based programmes exist [7, 8]. While recent meta-analyses provide some preliminary evidence of the positive impact of parent-implemented training programmes [9, 10], these reviews also show that many of these studies lack robust research designs and measures of treatment fidelity, and very few of these studies are contemporary and therefore potentially out of line with current approaches to speech and language therapy [9, 10]. Moreover, none of the studies reported look at outcomes for families for whom the language of intervention is not their first language. Indeed, Tosh et al. [10] exclude studies whose population included families that have English as a second language. This paper outlines the protocol for a feasibility study of the Talking Together programme: a two-staged intervention that offers universal screening of all 2-year-old children and then provides a home-visiting programme for children at risk of language difficulties. Importantly, the programme is designed to be used in a deprived multicultural community and delivered in the families’ home language. The programme aims to develop parents’ knowledge of the importance of a good language environment and helps to improve parent-child interaction with the specific aim of supporting children’s early language development.

The Talking Together programme was developed by BHT Early Education and Training and has been running in Bradford for a number of years. The programme has recently been commissioned by Better Start Bradford, one of five ‘A Better Start’ programmes across the UK, funded by the Big Lottery, with the specific aim of improving the outcomes of children in three areas: social and emotional development, nutrition and obesity, and communication and language development through a portfolio of commissioned services. Central to the work of Better Start Bradford is the collaboration with Born in Bradford (BiB), which enables robust evaluations of the commissioned services [11] and aligns the work with health services in the city of Bradford through BiB’s position as part of the Bradford Institute for Health Research (BIHR) based at Bradford Teaching Hospitals NHS Foundation Trust (BTHFT). The feasibility study described in this protocol takes the required steps towards a full effectiveness evaluation of the Talking Together intervention by establishing the acceptability and feasibility of conducting a trial, including the use of qualitative and quantitative methods to explore implementation. This study is referred to as the oTTer project (outcomes of the Talking Together evaluation and results) and is a collaboration between researchers at the University of York, University of Leeds, and Born in Bradford, and service providers at BHT Early Education and Training, with funding from the Nuffield Foundation.

### Research aims

The aim of the oTTer project is to establish the feasibility of a definitive RCT trial of Talking Together. There are two key objectives involved in meeting this aim:
To assess the feasibility of conducting a trial to evaluate the effectiveness of Talking Together including the acceptability of the intervention outcome measuresTo embed a qualitative evaluation within the oTTer trial to identify challenges with the implementation and delivery of the Talking Together programme as part of a trial

### Research questions

#### Aim 1

The research questions for aim 1 are as follows:
What are the recruitment and retention rates of Talking Together established by the number of participants who were identified, eligible, approached, consented, randomised, completed the programme, and followed up 6 months after baseline?How representative are the trial participants compared to the wider population receiving the intervention, based on key demographic indicators?What are the most appropriate outcome measures for a future definitive RCT, considering the acceptability, reliability, data quality (completeness), and responsiveness of administered measures?What is the sample size needed for a definitive trial based on data on intervention completion and attrition rates, along with outcome data group differences and variability across conditions?How acceptable are the intervention and trial procedures for practitioners and families, including randomisation and completion of outcome measures?

#### Aim 2

The research questions for aim 2 are as follows:
Was the intervention delivered with fidelity to the standardised procedures as measured by assessing the intervention content, and the frequency and duration of support received by participants?What are the time and resources required to train practitioners to administer the intervention, and how do these relate to resource requirements for definitive RCT development?

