### Recruitment and randomisation

#### Sample size

Based on existing recruitment data, over the 9-month period of recruitment, we would expect BHT Education and Training to screen approximately 670 families and refer approximately 250 families to the Talking Together programme, although not all of these families will be eligible for the trial or consent to take part. Recommendations for feasibility studies suggest that at least 30 participants per group will allow sufficient precision when estimating study summary measures [20, 21]. As such, our minimum required sample size is 60 families. However, we have set a desired sample size of 120 families, which is in excess of the recommended 60 participants for a feasibility study [14, 15], to allow for attrition and provide more confidence that a future definitive trial can be successfully conducted (see Fig. 1) [14]. Currently, all families within Better Start Bradford with children of 2 years of age are offered a language screening home visit. For the purposes of recruitment, the LDWs will provide families with an information sheet and consent form to take part in the trial at the end of these language screening visits if the family is going to be referred to Talking Together and meets the oTTer eligibility criteria. Families who consent to take part in the trial will then be randomly allocated to the intervention group or the waiting control group (see Fig. 2).

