#### Qualitative evaluation

For interviews, we will invite all LDWs and a purposive sample of oTTer families to participate. For service provider interviews, we are aiming to recruit a minimum of 50% of LDWs along with all members of the senior staff team involved with the Talking Together programme. For family interviews, we are aiming to recruit 20 to 30 oTTer families (10–15 from the intervention arm, and 10–15 in the waiting control arm) who are representative of the range of diversity in the sample. A purposive sampling framework based on key characteristics of families (e.g. main language spoken to child, ethnicity, group allocation, number of children in home) will be used to identify and invite families in the oTTer study to take part in interviews. Invitations will be made via the LDWs during a routine visit. Consent will be taken at the point of invitation, and it will be made clear that families will be contacted by a RA to arrange an interview. During this follow-up contact, families will be given the opportunity to withdraw consent to take part in the interview, and they will again be reminded of the right to withdraw prior to the start of the interview itself. Interviews will take place in the families own home.

All LDWs and senior staff with responsibility for Talking Together will be approached to take part in interviews once recruitment has finished. All LDWs (approx 15) and senior staff (*n* = 3) will receive a letter from the research team inviting them to participate in interviews. Interviews will be scheduled in discussion with the deputy language development programmes manager to ensure maximum participation with minimum disruption to service. The interviews will be carried out by a PDRA who has not previously worked with the BHT team and who can complete the interviews without the support of an interpreter.

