#### Secondary outcomes

In order to fully explore feasibility, there are a number of secondary outcomes:
Training and QA
Length of time taken to train staff to deliver Talking TogetherNumber of staff trained to deliver Talking TogetherProgramme delivery quality assurance (collected routinely by BHT)Data collection
Number, proportion, and timing of parent withdrawals from the Talking Together intervention and feasibility study and reasons for withdrawalNumber and proportion of parents with quantitative data at each time pointMissing item level data on intervention outcome measures at each time pointSample size estimation
Difference between arms and 95% confidence intervals for the two main child language measures (see the “Screening measures” section and “Intervention outcome measures” section below) at 6-month follow upAdherence and moderators
Based on Hasson [15], our evaluation will use quantitative and qualitative data to look at adherence and potential moderators. To measure adherence, we will collect data on frequency and number of sessions delivered, and completion rate of families. To explore potential moderators, we will obtain feedback on acceptability of trial procedures provided by parents, LDWs, and senior staff at BHT via interviews; feedback on the acceptability of the programme provided by parents via interview; feedback on ease of delivery of the programme provided by service providers via interview; and data on implementation fidelity through evaluation of quality assurance records.

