## Discussion

Recent reports have raised awareness of the need for increased early support for children with speech, language, and communication needs [1, 4]. Oral language difficulties have been linked with poor educational, employment, and mental health outcomes [4]. Research suggests that a strong foundation in language is fundamental to later language skills, and a corollary of this is that a communication-rich home language environment is key. However, the evidence for programmes that support parents in providing this strong foundation is lacking [6]. This programme of work is the first step towards developing a definitive randomised controlled trial to evaluate the effectiveness of one such programme: Talking Together. Designed and delivered by BHT Early Education and Training, the programme is one of a suite of services provided as part of the Better Start Bradford project and aims to improve children’s language outcomes through improving parent-child interactions. This study aims to inform the feasibility of delivery of a future definitive trial and as such will not provide evidence of effectiveness. However, it will provide invaluable information regarding the feasibility of using random allocation without adversely impacting on service delivery. It will identify the most effective measures to be used as primary and secondary outcomes (and how they can be administered), and through the qualitative work with service providers, it will identify any issues of implementation both for the service as a whole and for the service as part of the trial. Our qualitative work with families will help to identify barriers and facilitators to engaging with the Talking Together programme from an ethnically and socioeconomically diverse community. This increased understanding will lead to more informed commissioning decisions and service provision within Bradford and elsewhere, as well as providing the foundation for a large-scale RCT of the Talking Together programme.

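### The protocol names the between-arm difference observed in this feasibility study as a basis for the definitive sample size and names no other target effect; the estimate is too imprecise for that use

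*Protocol article*

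**What the plan says.** In the protocol article, Research questions (Aim 1), one question asks for the "sample size needed for a definitive trial based on data on intervention completion and attrition rates, along with outcome data group differences"; the same sentence goes on to list variability. Four inputs are therefore named: completion, attrition, the group difference and variability.

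Secondary outcomes has an entry for sample size estimation with a single item: "Difference between arms and 95% confidence intervals for the two main child language measures" at the 6-month follow-up. The two measures are CDI-Short and WellComm.

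The Sample size section relies on a recommendation that "at least 30 participants per group will allow sufficient precision when estimating study summary measures". From this it concludes that "our minimum required sample size is 60 families", and it adds that "we have set a desired sample size of 120 families".

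The Discussion states that the study is about feasibility and "as such will not provide evidence of effectiveness". The article gives no minimum important difference, no external effect size, and no rule for allowing for imprecision in the observed difference.

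**The concern.** Variability, attrition and completion are what a feasibility study can properly supply. The target difference is another matter: it should be the smallest effect worth detecting, or one supported by evidence from elsewhere. Here the only effect size mentioned in connection with the definitive sample size is the one that this small study will happen to observe, and the protocol itself disclaims that figure as evidence of effect.

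Required sample size varies with the inverse square of the target difference, so chance error in the difference is magnified. A difference that is high by chance gives a trial that is too small. One that is low by chance gives an oversized trial, and a zero or negative one gives no sample size at all. Sizing the next trial is one of this study's own research questions, so an unreliable input undermines that answer directly.

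**Working it through.** **The plan's own figure.** 2 × 30 = 60 families reproduces the stated minimum. It is a rule of thumb for the precision of summary measures, with no power calculation behind it. The desired 120 is 60 per arm under 1:1 allocation. At the 80% retention that counts as green under Progression criteria, 120 × 0.80 = 96, or 48 per arm.

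**Assumptions (not in the document).** True standardised difference d = 0.3, two-sided 5% test, 80% power, unadjusted comparison, SD = 1.

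**Sample size needed.** n per arm = 2 × ((1.96 + 0.84)/0.3)² ≈ 174.4, so 175.

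**Precision.** SE = √(2/n); half-width = 1.96 × SE.

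**Consequence of using the observed difference as the target.** If D is the observed difference, the planned n is 2 × (2.80/D)². The true power of that trial is then Φ(2.80 × d/D − 1.96), which falls below 50% when D > (2.80/1.96) × d = 1.43 × 0.3 ≈ 0.429. So P(true power < 50%) = 1 − Φ((0.429 − 0.3)/SE), and P(D ≤ 0) = Φ(−0.3/SE).

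| Analysed per arm | SE | 95% half-width | P(true power < 50%) | P(D ≤ 0) |
|---|---|---|---|---|
| 30 | 0.258 | ±0.51 SD | 31% | 12% |
| 48 | 0.204 | ±0.40 SD | 26% | 7% |
| 60 | 0.183 | ±0.36 SD | 24% | 5% |

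A simulation of 400,000 feasibility studies per scenario, which also estimated the SD, agrees closely. At 48 per arm, among studies with a favourable difference, the planned n per arm ran from 48 (10th percentile) to 1,558 (90th percentile), against 175 needed.

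**Sensitivity at 48 per arm** (simulation, given a favourable observed difference):
- 80% power target: P(true power < 50%) is 40%, 29%, 21% and 15% for true d of 0.2, 0.3, 0.4 and 0.5.
- 90% power target: 32%, 19%, 11% and 6%.

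**Baseline adjustment.** With an assumed pre-test to follow-up correlation of 0.6, the SE is multiplied by √(1 − 0.36) = 0.8. P(true power < 50%) at d = 0.3 and 80% power then becomes about 27% at 30 per arm and 19% at 60 per arm.

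**Comparison: target fixed, only the SD estimated.** If s is the estimated SD and σ the true one, true power at the target is Φ(2.80 × s/σ − 1.96). With 48 per arm (94 degrees of freedom), the 5th and 95th percentiles of s/σ are about 0.88 and 1.12, which gives power of about 69% and 88%. The chance of power below 50% is close to zero.

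**The case against.** The strongest reply is that the protocol never says the point estimate will be put into a sample size formula. It lists variability, attrition and completion as well, it asks for the difference with its 95% confidence interval, and Statistical analysis says the emphasis is on estimation, not testing. A later plan could still set a target on other grounds. Much of this stands: the figures above show what follows if the observed difference is used as the target, and are not a forecast of what the team will do. It does not dispose of the point. The text positively names the group difference as an input, makes it the sole item under sample size estimation, and offers no alternative target. A later plan would have to replace that input as well as add detail.

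It is also fair to say that the true effect of 0.3 SD is assumed, that baseline adjustment lowers the risk, and that with a large effect and a 90% power target the risk is small. These change the size of the problem, not its direction.

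Three stronger readings may tempt a reader, and the document does not support them:
- *A small observed difference would end the programme of trials.* Progression criteria cover recruitment (eligibility and consent), adherence to the assessment timeline and attrition. None uses the arm difference.
- *The primary outcome will be whichever measure shows the larger difference.* Responsiveness is one of several listed considerations and is not defined as a between-arm difference; it may mean change within children. Statistical analysis compares it between language groups.
- *The definitive sample size will ignore clustering by practitioner.* The article does not say so. It is silent, which is no error in a condensed article, and any design effect would rest wholly on assumed intraclass correlations and caseloads.

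**Conclusion.** The concern holds as a stated, poor choice of input. The observed arm difference is a named basis for the definitive sample size, no other target effect is named, and the study disclaims evidence on effectiveness. At 30 to 60 families per arm the difference is known only to within about ±0.51 to ±0.36 SD, so reaching the desired 120 families does not cure the problem. Used as the target, it would give a definitive trial with true power below 50% in roughly a quarter to a third of cases, and no usable sample size in 5% to 12%. Those figures rest on the assumed effect, test level and power, and on an unadjusted comparison.

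I rate it a should-fix. Recruitment is the primary outcome, and randomisation, data collection and the progression decision are unaffected. The data that a sound calculation needs are already to be collected.

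**What to change.** Reword the Aim 1 sample size question and the sample size entry under Secondary outcomes so that:
- the target difference for each candidate primary outcome is agreed on grounds of importance before outcome data are seen;
- this study supplies the SD (with its uncertainty allowed for, for example by using an upper confidence limit), the pre-test to follow-up correlation, attrition and completion;
- the arm difference with its 95% confidence interval is reported descriptively, and used only to check that the agreed target is not excluded.

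Recruitment has been open since October 2018, but no interim analysis is planned and analysis waits until all outcome data are in, so on the document's own timetable the target can still be set blind to results. No new data are needed. The cost is the rewording, some work to agree a target difference, and possibly a larger definitive trial.

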## Method

The protocol has been written in line with the SPIRIT checklist [12].

